| Hematology
Days 1, 8, and 15 before carfilzomib administration                                                                                                          | Hemoglobin, hematocrit, WBC count; WBC differential, red blood cell count, platelets. WBC differential may be automated or manual as per institutional standards.                                                                                                                                                                                                                                                                              |
| Complete Clinical Chemistry
Days 1, 8, and 15 before carfilzomib administration                                                                                         | Sodium, potassium, chloride, bicarbonate, BUN, creatinine, glucose, uric acid, total protein, albumin, calcium, phosphorus, magnesium, total bilirubin, alkaline phosphatase, ALT, AST, LDH. Results must be reviewed before dosing in Cycles 1 and 2.                                                                                                                                                                                         |
| Limited Clinical Chemistry
Days 2, 9, and 16 if clinically indicated                                                                                                    | Sodium, chloride, bicarbonate, BUN, creatinine, glucose, uric acid                                                                                                                                                                                                                                                                                                                                                                             |
| Pregnancy Test                                                                                                                                                             | FCBP with regular or no menstrual cycles must agree to have pregnancy tests every 7 days (weekly) for the first 28 days of study participation and then every 28 days while on study. If menstrual cycles are irregular, the pregnancy testing must occur weekly for the first 28 days and then every 14 days while on study.                                                                                                                  |

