### **6.3 Study Drug Administration**

#### **6.3.1 Carfilzomib Administration**

Carfilzomib for injection is supplied as a lyophilized parenteral product in single-use vials. The lyophilized product is reconstituted with water for injection to a final carfilzomib concentration of 2.0 mg/mL prior to administration. The dose will be calculated using the subject's actual BSA at baseline. Subjects with a BSA  $> 2.2 \text{ m}^2$  will receive a dose based upon a  $2.2 \text{ m}^2$  BSA. Dose adjustments do not need to be made for weight gains/losses of  $\leq 10\%$ . Subjects with a Body Surface Area (BSA) of greater than  $2.2 \text{ m}^2$  will receive a capped dose of 44 mg of carfilzomib (at the  $20 \text{ mg/m}^2$  dose level), 59.4 mg of carfilzomib (at the  $27 \text{ mg/m}^2$  dose level), or 79.2 (at the  $36 \text{ mg/m}^2$  dose level).

Carfilzomib will be given as an IV infusion over 30 minutes on Days 1, 2, 8, 9, 15 and 16 of Cycles 1- 8 and Days 1, 2, 15 and 16 of Cycles 9-24, and must be administered prior to daratumumab. If the subject has a dedicated line for carfilzomib administration, the line must be flushed with a minimum of 20 mL of normal saline prior to and after drug administration. The dose will be administered at a facility capable of managing hypersensitivity reactions. Subjects will be pre-hydrated with 250mL normal saline or other appropriate IV fluid formulation on cycle 1 Day 1. Other hydration procedures will be optional and per the discretion of the treating investigator. Subjects will remain at the clinic under observation for at least 1 hour following each dose of carfilzomib in Cycle 1 and following the dose on Cycle 2, Day 1. Subjects should be monitored periodically during this period for evidence of fluid overload. Serum chemistry values, including creatinine, must be obtained and reviewed prior to each dose of carfilzomib during Cycles 1 and 2. Refer to [Table 6-8](#) for guidance regarding dose reduction in subjects with compromised renal function.

Doses of carfilzomib may be rescheduled up to 2 days if the scheduled day falls upon a holiday or with approval from the Lead Principal Investigator. If Day 2 of Carfilzomib dosing is delayed (i.e., Day 2, 9, 16) 4 mg of dexamethasone premedication is required to be used prior to second treatment. Missed doses will not be replaced during a cycle. Carfilzomib will be escalated from  $20 \text{ mg/m}^2$  (Cycle 1 Days 1 and 2)

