#### **6.4 Instructions for Initiation of a New Cycle**

A new course of treatment may begin on the scheduled Day 1 of a new cycle if all of the following are met:

- $ANC \geq 1.0 \times 10^9/L$
- Platelet count  $\geq 30 \times 10^9/L$
- Any other study drug-related adverse event must have resolved to Grade 1 or baseline (see Appendix 2)
- Serum uric acid and creatinine concentrations must return to baseline prior to carfilzomib doses during Cycles 1 and 2

If  $ANC < 1.0 \times 10^9/L$  but  $> 0.75 \times 10^9/L$ , the start of a new cycle is at the discretion of the treating investigator

If these conditions are not met on Day 1 of a new cycle, the subject will be evaluated weekly, and a new treatment cycle will not be initiated until the toxicity has resolved, as described above.

If daratumumab, carfilzomib, or lenalidomide, or daratumumab are held for the remainder of the previous cycle or the new cycle is delayed due to residual toxicity on the planned Day 1 of the next cycle, then the new cycle will be started at 1 dose decrement.

If a delay of starting a new cycle is greater than 21 days, the subject should be discontinued from treatment, unless continuing treatment is mutually agreed upon by the site Lead Principal Investigator at the University of Chicago and the co-investigator at the treating institution.

Dexamethasone may be discontinued without the subject discontinuing study treatment.

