**Table 6-6 Dose Modification Guidelines for Hematologic Toxicities**

| When Platelets:                                                                                                                                                                                                                              | Lenalidomide                                                                                                                                                                                                                                   | Carfilzomib                                                     |                                                                                                                 |
|----------------------------------------------------------------------------------------------------------------------------------------------------------------------------------------------------------------------------------------------|------------------------------------------------------------------------------------------------------------------------------------------------------------------------------------------------------------------------------------------------|-----------------------------------------------------------------|-----------------------------------------------------------------------------------------------------------------|
| Fall to $< 30 \times 10^9/L$                                                                                                                                                                                                                 | 
 
• Hold dose, follow CBC weekly
 
• Hold prophylactic anticoagulation until platelets return to <math>\geq 30 \times 10^9/L</math>
 
• Then resume at 1 dose decrement
 
          | If platelets $10-30 \times 10^9/L$ without evidence of bleeding | 
 
• Hold
 
• With resolution restart at previous dose
 
    |

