**Table 6-7 Dose Modification Guidelines for Hematologic Toxicities**

| When ANC:                                   | Lenalidomide                                                                                                               | Carfilzomib              |                                                                                 |
|----------------------------------------------------|-----------------------------------------------------------------------------------------------------------------------------------|---------------------------------|---------------------------------------------------------------------------------|
| Fall to $< 0.75 \times 10^9/L$                     | Hold dose, administer myeloid growth factor
Follow CBC weekly
Resume at full dose when $ANC \geq 0.75 \times 10^9/L$        | If ANC $0.5-0.75 \times 10^9/L$ | Continue at full dose                                                           |
|                                                    |                                                                                                                                   | If ANC $< 0.5 \times 10^9/L$    | Hold
Resume at 1 dose decrement when ANC returns to $\geq 0.5 \times 10^9/L$ |
| For each subsequent drop to $< 0.75 \times 10^9/L$ | Hold dose, administer myeloid growth factor
Follow CBC weekly
Resume at 1 dose decrement when $ANC \geq 0.75 \times 10^9/L$ | If ANC $0.5-0.75 \times 10^9/L$ | Continue at full dose                                                           |
|                                                    |                                                                                                                                   | If ANC $< 0.5 \times 10^9/L$    | Hold
Resume at 1 dose decrement when ANC returns to $\geq 0.5 \times 10^9/L$ |

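### Four rows of Table 6-8 release a hold at Grade 2 where 6.4 and 6.5 require Grade 1 or baseline, and for painful Grade 2 neuropathy the hold requires no recovery; secondarily, the restart dose after a delayed Day 1 is stated two ways

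*Protocol*

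**What the plan says.** **Recovery grade.** Protocol 6.4 lists the conditions for starting a new cycle. Beyond the ANC and platelet limits it requires: "Any other study drug-related adverse event must have resolved to Grade 1 or baseline". Section 6.5 allows study treatment to be reintroduced if the event is back to baseline or to Grade 1 or lower within 21 days, and otherwise requires permanent discontinuation. A separate sentence in 6.5 applies the Grade 1 or baseline limit to every clinically significant non-hematologic toxicity. Table 6-8 then gives event-specific rows. Four of them release the hold at Grade 2 or lower: neuropathy for both lenalidomide and carfilzomib, and, for carfilzomib only, CrCl below 30 mL/min requiring dialysis, hypertension, and pulmonary hypertension.

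**Restart dose.** If a drug was held for the rest of the previous cycle, or residual toxicity delays Day 1, 6.4 says "then the new cycle will be started at 1 dose decrement". It states no exception, does not limit the step-down to the drug that was held, and includes daratumumab. For carfilzomib with platelets of 10-30 × 10⁹/L and no bleeding, Table 6-6 says "With resolution restart at previous dose". For lenalidomide at the first ANC fall below 0.75 × 10⁹/L, Table 6-7 says "Resume at full dose when" the ANC is at least 0.75 again. Neither row is limited to the current cycle.

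**The concern.** A site treating a patient with one of the four toxicities finds two recovery thresholds and nothing that says which governs. Neuropathy is the case that matters most for the patient. The table lets both drugs continue, one level lower, while painful Grade 2 neuropathy is unchanged. The text of 6.5 requires improvement first and, failing that within 21 days, permanent discontinuation. These are opposite instructions for the same patient.

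The dose inconsistency matters less. When toxicity delays Day 1, one patient state has two written doses, and two sites can each follow the protocol and give different ones. A reduction can persist, because later cycles of carfilzomib and lenalidomide run at the best tolerated dose (6.3.1, 6.3.2).

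**Working it through.** No figure in the plan is at issue, so the check sets the rules side by side.

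**1. Recovery grade, row by row**

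| Table 6-8 row | Drug | Hold starts at | Row releases at | 6.4 and 6.5 release at |
|---|---|---|---|---|
| Neuropathy | both | Grade 2 with pain, or any Grade 3 | Grade 2 or lower | Grade 1 or baseline |
| CrCl < 30 mL/min on dialysis | carfilzomib | the condition itself | Grade 2 or lower | Grade 1 or baseline |
| Hypertension | carfilzomib | Grade 3 or higher | Grade 2 or lower | Grade 1 or baseline |
| Pulmonary hypertension | carfilzomib | Grade 3 or higher | Grade 2 or lower | Grade 1 or baseline |

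Four rows differ from the general rule. All four restart one dose level lower, so here the conflict is over when to restart and not over the dose.

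**2. The neuropathy hold.** Painful Grade 2 starts the hold. The release is Grade 2 or lower, which that patient already meets, so the only operative instruction is the decrement. For Grade 3 the hold does work, since the patient must fall to Grade 2. If that Grade 2 is painful, however, the patient meets the release and the trigger together.

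**3. Can a Grade 2 baseline reconcile the rules?**
- Neuropathy: no. Exclusion 10 bars Grade 2 or higher at screening, so baseline is at most Grade 1.
- Hypertension: in some patients. Exclusion 19 bars only uncontrolled hypertension.
- Pulmonary hypertension: possibly in some patients, since section 5.2 has no criterion for it.

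**4. The 21-day clause.** Take a patient still at Grade 2 neuropathy after 21 days. The table row restarts at one decrement; 6.5 discontinues permanently unless the Lead Principal Investigator approves a deviation.

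**5. Restart dose when Day 1 is delayed.**
- Platelets 20 × 10⁹/L, no bleeding, on Day 1: 6.4 needs at least 30, so the cycle is delayed. After recovery Table 6-6 gives carfilzomib at the previous dose, 36 mg/m² if nominal; 6.4 gives 27 mg/m² (Table 6-2).
- ANC 0.6 × 10⁹/L on Day 1, first fall: 6.4 needs 1.0, or more than 0.75 at the investigator's discretion, so the cycle is delayed. After recovery Table 6-7 gives lenalidomide at full dose, 25 mg if nominal; 6.4 gives 20 mg (Table 6-3).

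Other rows with no time limit raise the same question if Day 1 is delayed. Tumor lysis, Grade 3-4 infection without neutropenia, and herpes restart both drugs at full dose. Several rash, arrhythmia and allergic-reaction rows restart carfilzomib at its current dose.

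**6. Size of one decrement from nominal.**
- Carfilzomib: 6 × 36 = 216 against 6 × 27 = 162 mg/m² per six-dose cycle; 4 × 36 = 144 against 4 × 27 = 108 per four-dose cycle; 9/36 = 25% lower.
- Lenalidomide: 21 × 25 = 525 against 21 × 20 = 420 mg per cycle; 5/25 = 20% lower.

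**The case against.** **On grade.** A specific row can be read as an exception to a general rule, and the reintroduction sentence in 6.5 follows one about discretionary holds, so it might cover only those. That reading does not clear the conflict: the later sentence in 6.5 on all clinically significant non-hematologic toxicities has no such limit, and no row is named as an exception. It is fair that drug-related neuropathy must still reach Grade 1 or baseline before the next cycle under 6.4, which limits dosing at Grade 2 to the rest of the current cycle.

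**On dose.** Section 6.4 concerns starting a cycle, and several lenalidomide rows are expressly limited to restarts before Day 21. The thyroid row, which does speak of the next cycle, agrees with 6.4. So the tables can be read as governing restarts within a cycle, with 6.4 adding a step at cycle start. That is workable and probably intended, and within a cycle there is no conflict. But the protocol does not say it, and the rows in question carry no such limit. The note under Table 6-6 also lets the investigator give carfilzomib in Grade 4 thrombocytopenia without bleeding, so some variation between sites is by design. It sets no restart dose and does not lift the Day 1 platelet limit in 6.4.

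**A stronger reading to avoid.** Carfilzomib dosing in Cycles 1-8 ends on Day 16 ("Carfilzomib will be given as an IV infusion over 30 minutes on Days 1, 2, 8, 9, 15 and 16"), and "Missed doses will not be replaced during a cycle". A reader might infer that any hold found on Day 15 triggers the 6.4 decrement while the same event on Day 8 does not. The documents do not settle this. Section 6.4 does not say whether omitting only the Day 15 and 16 doses counts as a hold for the rest of the cycle, and its phrase about residual toxicity on Day 1 can be read as qualifying both limbs of the sentence.

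**Lead Principal Investigator clauses.** Section 6.5 sends departures from the stated modifications to one person, which limits divergence. Where both doses are written in the protocol, a site following either has no evident departure to report.

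**Conclusion.** The restart-grade contradiction stands. Four rows of Table 6-8 release at Grade 2 against Grade 1 or baseline in 6.4 and 6.5, and the neuropathy hold is empty for painful Grade 2. Baseline cannot explain neuropathy; it may remove the conflict in some patients with hypertension or pulmonary hypertension.

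The restart-dose inconsistency stands in a narrower form. It arises where toxicity delays Day 1 and the table row has no time limit, and it amounts to one dose level (25% for carfilzomib, 20% for lenalidomide, from nominal). It would be wrong to say that whole table cells contradict 6.4.

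The mention of daratumumab in the 6.4 sentence is editorial, since 6.3.5, 6.5 and 6.5.1.1 already fix its dose.

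Severity is minor. A reader might infer that the Cycle 8 sCR/MRD rate is distorted; the documents do not support that. They give no event frequencies, no analysis or endpoint definition depends on these rules, and 6.3.5 says there are no new starts, so the number of patients affected may be small.

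**What to change.** 1. Neuropathy row of Table 6-8: hold both drugs until Grade 1 or baseline, then restart at one decrement.
2. Dialysis, hypertension and pulmonary hypertension rows: align the release with 6.5, or name them as exceptions in both 6.4 and 6.5.
3. In 6.4, state that its decrement governs the start of a new cycle, for the held drug only, and that Tables 6-6 to 6-8 govern restarts within a cycle; or name the rows exempt from the decrement. The same sentence can say whether omitting only the Day 15 and 16 carfilzomib doses counts as a hold to the end of the cycle.
4. Delete daratumumab from the decrement sentence in 6.4.

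The cost is wording in 6.4, 6.5 and up to four rows of Table 6-8 at the next amendment, plus a memo to sites. No procedures or patients are added.

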## 6.5 Dose-modification guidelines

The following sections and tables summarize dosing modifications of daratumumab, carfilzomib, lenalidomide and dexamethasone to manage possible toxicity. Dose modifications different from those stated in the protocol should be discussed with the Lead Principal Investigator. Administration of daratumumab, carfilzomib and lenalidomide will be discontinued in the event of any other toxicity that, in the opinion of the lead, secondary site, or treating investigator, warrants discontinuation.

In addition to dose reductions, administration of daratumumab, carfilzomib and lenalidomide will be held temporarily in the event of a treatment-related toxicity at the treating investigator's discretion.

Study treatment may be reintroduced if resolution of the event to the baseline value or to  $\leq$  Grade 1 within 21 days; otherwise study drug will be permanently discontinued. Any deviations from this plan must be approved by the Lead Principal Investigator.

All clinically-significant non-hematologic toxicities must be resolved to Grade 1 or baseline.

Individual dose modification of daratumumab is not permitted. Dosing can be delayed to manage daratumumab-related toxicities. Dose de-escalation of daratumumab will be based only on the Data and Safety Monitoring Board (DSMB) recommendation. Dose reduction levels of carfilzomib, lenalidomide and dexamethasone for toxicity management of individual subjects are provided below:

**Table 6-2 Dose Reductions for Carfilzomib**

| Nominal carfilzomib dose | Dose -1       | Dose -2       | Dose -3       | Dose -4       |
|---------------------------------|----------------------|----------------------|----------------------|----------------------|
| 36 mg/m             | 27 mg/m  | 20 mg/m  | 15 mg/m  | 11 mg/m  |

**Table 6-3 Dose Reductions for Lenalidomide**

| Nominal Lenalidomide Dose | Dose -1 | Dose -2 | Dose -3 | Dose -4 | Dose -5       |
|----------------------------------|----------------|----------------|----------------|----------------|----------------------|
| 25 mg Days 1-21                  | 20 mg          | 15 mg          | 10 mg          | 5 mg           | 5 mg every other day |

**Table 6-4 Dose Reductions for Dexamethasone**

| Nominal
Dexamethasone Dose | Dose -1 | Dose -2 | Dose -3 |
|---------------------------------------|----------------|----------------|----------------|
| 40 mg                                 | 32 mg          | 24 mg          | 20 mg          |
| 20 mg                                 | 12 mg          | 8 mg           | 4 mg           |

\*Split dosing of dexamethasone on Days 1, 2, 8, 9, 15, 16, 22, 23 may be implemented to control toxicities that do not require a dose reduction. Split dosing requires the approval of the Lead Principal Investigator before implementing.

### **6.5.1 Toxicity Management Guidelines**

Treatment guidelines for specific hematologic toxicities are outlined in Section 6.5.1.1 and non-hematologic toxicities in Section 6.5.1.2. In addition to dose reductions, administration of daratumumab, carfilzomib and/or lenalidomide may be held temporarily in the event of a treatment-related toxicity at the treating investigator's discretion.

#### **6.5.1.1 Toxicity Management for Daratumumab**

##### Infusion-Related Reactions

Infusion-related reactions (IRRs) are systemic reactions related to daratumumab administration. Participants should be observed carefully during daratumumab administrations. Trained study staff at the clinic should be prepared to intervene in case of any IRRs, and resources necessary for resuscitation (e.g., agents such as epinephrine and aerosolized bronchodilator, medical equipment such as oxygen tanks, tracheostomy equipment, and a defibrillator) must be available at the bedside. Attention to staffing should be considered when multiple participants will be dosed at the same time. If an IRR develops during Dara SC administration, then the administration should be temporarily interrupted. Participants who experience AEs during Dara-SC administration must be treated for their symptoms. Participants should be treated with paracetamol (acetaminophen), antihistamine, or corticosteroids, as needed. Intravenous saline may be indicated. For bronchospasm, urticaria, or dyspnea, participants may

require antihistamines, oxygen, corticosteroids, or bronchodilators. For hypotension, participants may require vasopressors. In the event of a life-threatening IRR (which may include pulmonary or cardiac events) or an anaphylactic reaction, Dara-SC should be discontinued.

